## Abstract

**Background:**

Coronavirus disease 2019 (COVID-19), caused by a novel corinavirus (later named SARS-CoV-2 virus), was fistly reported in Wuhan, Hubei Province, China towards the end of 2019. Large-scale spread within China and internationally led the World Health Organization to declare a Public Health Emergency of International Concern on 30^th^ January 2020. The clinical manifestations of COVID-19 virus infection include asymptomatic infection, mild upper respiratory symptoms, severe viral pneumonia with respiratory failure, and even death. There are no antivirals of proven clinical efficacy in coronavirus infections. Remdesivir (GS-5734), a nucleoside analogue, has inhibitory effects on animal and human highly pathogenic coronaviruses, including MERS-CoV and SARS-CoV, in in vitro and in vivo experiments. It is also inhibitory against the COVID-19 virus in vitro. The aim of this study is to assess the efficacy and safety of remdesivir in adult patients with severe COVID-19.

**Methods:**

The protocol is prepared in accordance with the SPIRIT (Standard Protocol Items: Recommendations for Interventional Trials) guidelines. This is a phase 3, randomized, double-blind, placebo-controlled, multicentre trial. Adults (≥ 18 years) with laboratory-confirmed COVID-19 virus infection, severe pneumonia signs or symptoms, and radiologically confirmed severe pneumonia are randomly assigned in a 2:1 ratio to intravenously administered remdesivir or placebo for 10 days. The primary endpoint is time to clinical improvement (censored at day 28), defined as the time (in days) from randomization of study treatment (remdesivir or placebo) until a decline of two categories on a six-category ordinal scale of clinical status (1 = discharged; 6 = death) or live discharge from hospital. One interim analysis for efficacy and futility will be conducted once half of the total number of events required has been observed.

**Discussion:**

This is the first randomized, placebo-controlled trial in COVID-19. Enrolment began in sites in Wuhan, Hubei Province, China on 6^th^ February 2020.

**Trial registration:**

ClinicalTrials.gov: NCT04257656. Registered on 6 February 2020.

## Introduction

### Background and rationale {6a}

In December 2019, Wuhan City, Hubei Province experienced an outbreak of pneumonia of unknown cause. On 7^th^ January 2020, a previously unidentified betacoronavirus, later named SARS-CoV-2 virus (or the disease named COVID-19), was identified by the Chinese Center for Disease Control and Prevention (China CDC) as the aetiological agent [1]. The SARS-CoV-2 probably derived originally from bats, and amongst coronaviruses known to infect humans, is most closely related to, but distinct from, the SARS coronavirus. The clinical manifestations of COVID-19 virus infection include asymptomatic infection, mild upper respiratory symptoms, severe viral pneumonia with respiratory failure, and even death. Although the risk of severe illness is not yet clear, hospitals in areas with significant community transmission have experienced a major increase in the number of hospitalized pneumonia patients, with the frequency of severe disease in hospitalized patients being as high as 30% [2–4]. The progression from prodromes (usually fever, fatigue, and cough) to severe pneumonia requiring oxygen support, mechanical ventilation, or extracorporeal membrane oxygenation (ECMO) is most commonly seen in the second week following onset of symptoms of a viral infection [2]. The kinetics of viral replication in the respiratory tract has not been well characterized, but this relatively slow progression provides a potential time window and opportunity for antiviral therapies to influence the course of the disease.

Remdesivir (GS-5734) is a monophosphoramidate prodrug of an adenosine analogue (GS-441524) and has broad action against a range of RNA viruses [5]. It has been identified as the most promising therapeutic agent for evaluation in the treatment of COVID-19 by an expert committee convened by the WHO R&D Blueprint [6]. The primary mechanism of action is the intracellular incorporation of the pharmacologically active nucleoside triphosphate form into nascent RNA chains by the viral RNA-dependent RNA polymerase, causing premature RNA chain termination [7–9]. In vitro experiments have shown that remdesivir inhibits bat coronaviruses, endemic human coronavirus (OC43, 229E), and the human pathogenic coronaviruses MERS-CoV, SARS-CoV, and COVID-19 [10–13]. Remdesivir has shown preventive and therapeutic effects in a mouse model of SARS-CoV [10]. In a MERS-CoV mouse model, prophylactic and therapeutic administration of remdesivir improved lung function, decreased lung viral load, and reduced severe lung pathological findings [14]. Remdesivir has also shown prophylactic efficacy in MERS-CoV-infected Indian rhesus monkeys (personal communication: Gilead Sciences, Inc.).

Evaluation of intravenously administered remdesivir tolerance and safety in 94 healthy adult volunteers has found it to be generally well tolerated and to have an acceptable safety profile. The only significant adverse effects were transient grade 1 or grade 2 increases in aspartate transaminase (AST) and alanine transaminase (ALT) (personal communication: Gilead Sciences, Inc.). Further clinical experience was obtained through a randomized controlled trial in patients with Ebola virus disease. In this trial 175 patients received intravenous remdesivir with a loading dose on day 1 (200 mg in adults, and adjusted for body weight in pediatric patients), followed by a daily maintenance dose (100 mg in adults) starting on day 2 and continuing for 9 to 13 days. The only reported serious adverse event (SAE) was that of one patient who experienced hypotension that resulted in cessation of the remdesivir loading dose, followed rapidly by cardiac arrest. However, the cause of death could not be distinguished from the patient’s underlying severe Ebola virus disease [15].

Given the in vitro and in vivo effectiveness of remdesivir against a range of pathogenic human coronaviruses and the acceptable tolerance and safety in humans, we developed this trial with the objective of evaluating the safety and efficacy of intravenous remdesivir in adults with severe COVID-19.

## Objectives {7}

The trial objective is to evaluate the efficacy and safety of intravenous remdesivir combined with standard of care compared with standard care alone in adult patients with severe COVID-19.

### Trial design {8}

This is a phase 3, parallel group, randomized, double-blind, placebo-controlled, superiority, multicentre trial. The allocation ratio is 2:1 in favour of remdesivir to maximize learning about the experimental treatment whilst allowing a wider pool of patients access to the experimental treatment in order to support recruitment.

## Methods: participants, interventions, and outcomes

### Study setting {9}

The setting involved hospitals in Wuhan city, Hubei Province, People’s Republic of China. Study sites included Jin Yin-tan Hospital, Tongji Hospital, Tongji Medical College of Huazhong University of Science & Technology, Wuhan Lung Hospital, the Central Hospital of Wuhan, Zhongnan Hospital of Wuhan University, Renmin Hospital of Wuhan University, Union Hospital, Tongji Medical College of Huazhong University of Science & Technology, Wuhan First Hospital, Wuhan Third Hospital, and Wuhan Fourth Hospital.

### Eligibility criteria {10}

#### Inclusion criteriaThe inclusion criteria are as follows:

Age ≥ 18 years at time of signing of informed consent formLaboratory (reverse transcription polymerase chain reaction [RT-PCR])-confirmed COVID-19Pneumonia confirmed with chest imagingHospitalized with SPO2 ≤ 94% on room air or PaO2/FiO2 ≤ 300 mmHg≤ 12 days since symptoms onsetWillingness of study participant to accept randomization to any assigned treatment armMales and females of child-bearing age must agree to use effective birth control measures (hormone method, barrier method, or abstinence) during the trial and at least 7 days after the last medication doseMust agree not to enrol in any other study of an antiviral agent prior to completing the 28-day follow-up.

#### Exclusion criteriaThe exclusion criteria are as follows:

Physician makes a decision that trial involvement is not in patient’s best interest, or patient has any condition that does not allow the protocol to be followed safelyKnown severe liver disease (e.g. cirrhosis, ALT > 5 × upper limit of normal (ULN), or AST > 5 × ULN)Patients who are pregnant or breastfeeding, or positive pregnancy test in women of childbearing agePatients with known severe renal impairment (estimated glomerular filtration rate ≤ 30 ml/min/1.73 m^2^), or patients receiving continuous renal replacement therapy, haemodialysis, or peritoneal dialysisWill be transferred to any other hospital which is not a study site within 72 hReceipt of any investigational treatment for COVID-19 within 30 days prior to screening.

#### Who will take informed consent? {26a}

Informed consent will be obtained from eligible patients or their substitute decision-makers (for patients lacking decision-making capacity) by study physicians or other trial staff with delegated responsibility.

### Additional consent provisions for collection and use of participant data and biological specimens {26b}

The consent form includes provisions for research data and samples and residual clinical blood samples to be stored for future scientific research on COVID-19.

### Interventions

#### Explanation for the choice of comparators {6b}

The active arm is intravenously administered remdesivir in addition to routine supportive care. Remdesivir was chosen for evaluation because of its in vitro activity against SARS-CoV, MERS-CoV, and SARS-CoV-2, and its in vitro activity against SARS-CoV and MERS-CoV. There are safety data for remdesivir in healthy human volunteers and individuals with Ebola virus disease. These data suggest that remdesivir is generally well tolerated and has an acceptable safety profile. It has been identified as the most promising therapeutic agent for treatment of COVID-19 by the WHO R&D Blueprint [6]. The dose of remdesivir was selected on the recommendation of Gilead Sciences, Inc., based on known pharmacokinetics and dose-ranging studies in healthy volunteers. The control arm is placebo in addition to routine supportive care. There are no proven antiviral therapies for SARS-CoV-2 to include as an active control comparator.

#### Intervention description {11a}

#### The intervention is described as follows for the experimental and control groups:

Group A (experimental group)
Loading dose: Remdesivir 200 mg in 350 ml normal saline (0.9% sodium chloride) single daily dose infused intravenously over approximately 30–60 min (with a target time of 30 min) for 1 dayMaintenance dose: Remdesivir 100 mg in 250 ml normal saline (0.9% sodium chloride) single daily dose infused intravenously over approximately 30–60 min (with a target time of 30 min) for 9 days.Group B (control group)
Loading dose: Placebo in 350 ml normal saline (0.9% sodium chloride) single daily dose infused intravenously over approximately 30–60 min (with a target time of 30 min) for 1 dayMaintenance dose: Placebo in 250 ml normal saline (0.9% sodium chloride) single daily dose infused intravenously over approximately 30–60 min (with a target time of 30 min) for 9 days.

### Criteria for discontinuing or modifying allocated interventions {11b}

The discontinuation/modification criteria are as follows:
Any serious or intolerable adverse event (AE) which, in the investigators’ judgement, requires withdrawal of the subject from the study. This may include drug intolerance or an unacceptable AE; any severe grade 4 AE, regardless of whether the AE is considered likely related to the study drug or not; significant results of laboratory tests which may require withdrawal of the participant, at the discretion of the researchers and the clinician; allergic reactions (including oropharyngeal oedema, severe rash, bronchospasm, and immediate-type allergic reactions); acute hepatitis;^1^ stage III or above acute kidney injuryInvestigator request for the subject to be withdrawn from the study.

### Strategies to improve adherence to interventions {11c}

This item is not applicable, since active agent and placebo are administrated intravenously by healthcare professionals.

### Relevant concomitant care permitted or prohibited during the trial {11d}

This study seeks to evaluate the effect of remdesivir in addition to standard of care alone, rather than an effect that might be altered by other experimental treatments. Therefore, all concomitant care and interventions are permitted other than concomitant receipt of any other experimental treatment.

#### Provisions for post-trial care {30}

No special arrangements for post-trial care are anticipated.

### Outcomes {12}

#### Primary outcome measure

The primary outcome measure is time to clinical improvement (TTCI) (censored at day 28).

TTCI is defined as the time (in days) from randomization of study treatment (active or placebo) until a decline of two categories on a six-category ordinal scale of clinical status (1 = hospital discharge; 2 = hospitalization, not requiring supplemental oxygen; 3 = hospitalization, requiring supplemental oxygen (but not non-invasive mechanical ventilation [NIV]/high-flow nasal cannula [HFNC] therapy); 4 = hospitalization, requiring NIV and/or HFNC therapy; 5 = hospitalization, requiring ECMO and/or invasive mechanical ventilation [IMV]; 6 = death) or live hospital discharge, whichever comes first.

#### Secondary outcome measures:The secondary outcome measures are the following:

Percentage of subjects in each clinical category on the six-category ordinal scale (time frame: days 7, 14, 21, and 28)Time to disease improvement, defined as the time to hospital discharge, or NEWS2 (National Early Warning Score 2) of ≤ 2 maintained for 24 h (time frame: up to 28 days)All-cause mortality (time frame: up to 28 days)Duration (days) of IMV (time frame: up to 28 days)Duration (days) of supplemental oxygenation (time frame: up to 28 days)Length of hospital stay (days) (time frame: up to 28 days)Incidence of nosocomial secondary infectionTime to SARS-CoV-2 virus RT-PCR negativity in upper and lower respiratory tract specimens (time frame: up to 28 days)Change (reduction) in SARS-CoV02 viral RNA load in upper and lower respiratory tract specimens as assessed by area under viral load curve (time frame: up to 28 days)Pharmacokinetic parameters of remdesivir or its active metabolitesFrequency of SAEs (time frame: up to 28 days).

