### Sample size {14}

The primary outcome is TTCI (censored at day 28). An interim analysis for futility and efficacy is planned at the midpoint of the trial. At this point the sample size may also be re-assessed. A one-sided type I error of 2.5% across the two stages of the trial and a power of 80% if the hazard ratio comparing remdesivir to placebo is 1.4 is used. This hazard ratio corresponds to a reduction in TTCI to 15 days on remdesivir if the TTCI on standard of care was 21 days. Triangular boundaries [16] are used to account for the multiple looks at the data, and allowance for the 2:1 randomization in favour of remdesivir is made. Under these assumptions, the total number of events required in this study is 325.

Assuming an 80% event rate within 28 days across both arms and a dropout rate of 10% implies that approximately 453 patients are to be recruited for this trial (151 on placebo and 302 on remdesivir).

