### Assignment of interventions: allocation

#### Sequence generation {16a}

A permuted block (30 patients per block) randomization sequence, including stratification, is prepared by a statistician not involved in the trial using SAS software, version 9.4 (SAS Institute). Patient randomization is stratified based on respiratory support methods at the time of enrolment: (1) no oxygen support, oxygen support with nasal duct or mask; (2) high-flow oxygen, NIV, IMV/ECMO.

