### Data collection and management

#### Plans for assessment and collection of outcomes {18a}

Investigators are responsible for assessment and collection of outcome, baseline, and other trial data, and the data are double checked by the clinical research coordinators and clinical research associates as well as data managers. Nasopharyngeal/oropharyngeal swabs, lower respiratory tract specimens (sputum/tracheal aspirate/bronchial alveolar lavage fluid), feces/anal swabs, and pharmacokinetic samples (whole blood) will be sent to a central laboratory, where tests will performed according to laboratory standard operating procedures (SOPs). Data collection forms can be found at https://edc.clinflash.net/login.

For the efficacy outcome measures, two scales (six-category ordinal scale of clinical status and NEWS2) are used. Investigators will be trained to use these scales.

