### Statistical methods

#### Statistical methods for primary and secondary outcomes {20a}

The primary outcome is TTCI up to day 28 of patients on remdesivir compared to patients receiving placebo. Patients will be randomized at a ratio of 2:1 to receive either remdesivir or placebo. All reporting will adhere to the Consolidated Standards of Reporting Trials (CONSORT) guideline as well as the corresponding extension for adaptive clinical trials [17, 18].

The final analysis of the primary endpoint will use a Cox proportional hazards model following the intention-to-treat principle. The final analysis will be conducted once a total of 325 events have occurred across both treatment groups. Under the assumption of an 80% event rate within 28 days and accounting for 10% dropout, this means that the maximum number of patients to be recruited is approximately 453. A standardized test statistic is then found on the basis of this model—if this test statistic exceeds 2.095, then it will be concluded that remdesivir is significantly better than placebo. Median unbiased effect estimates and confidence intervals accounting for the interim analysis will be reported [19]. Analysis of secondary endpoints will use a logistic model for binary variables such as mortality and a Cox proportional hazards model for time-to-event endpoints. A statistical analysis plan (SAP) providing all details of the analyses to be undertaken will be completed before any data analysis will be conducted.

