During epidemics, as well as calls to treat everyone, other voices demand that vulnerable patients not be treated as ‘guinea pigs’. Clinical trials use well-deliberated, tested, and transparent scientific methods, and are undertaken as a joint endeavour between patients and health professionals within a clear ethical framework. Health emergencies raise additional ethical concerns, but these have been carefully considered by various groups, and clear guidance exists on the conduct of clinical research during health emergencies [20–22].

The choice of the primary endpoint for a clinical trial is always challenging, but it has added difficulties when dealing with a disease with uncertain natural history, an overstretched workforce, and the desire for an early answer. This requires an endpoint that is clinically meaningful, is based on simple data collection, has sufficient power, and will occur early. It also requires statistical methods that are robust to misspecification of design parameters, such as the endpoint frequency. We believe that our primary endpoint is both pragmatic and informative, but we have included a range of secondary endpoints to show consistency with the primary endpoint, as recommended by the US Food and Drug Administration for trials in influenza [23].

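### Time to disease improvement uses an absolute NEWS2 threshold with no baseline rule, so a patient already at or below 2 at randomisation can count as improved without changing

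*Protocol article*

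**What the plan says.** All references are to the protocol article.

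- **Secondary outcome measures.** Time to disease improvement is met by discharge from hospital or by a "NEWS2 (National Early Warning Score 2) of ≤ 2 maintained for 24 h". The NEWS2 limb is a level to be reached and held; baseline does not enter the definition.
- **Eligibility criteria {10}.** Severity at entry is set by imaging-confirmed pneumonia together with an oxygenation criterion (SpO2 of 94% or less on room air, or PaO2/FiO2 of 300 mmHg or less). Neither the inclusion nor the exclusion list mentions NEWS2.
- **Sequence generation {16a}.** The milder stratum is "1) no oxygen support, oxygen support with nasal duct or mask", so patients on room air are expected in the trial.
- **Plans for assessment and collection of outcomes {18a}.** For efficacy, "two scales (six-category ordinal scale of clinical status and NEWS2) are used". NEWS2 is not used for entry or stratification.
- **Statistical methods {20a}.** Secondary outcomes of this kind are analysed with "a Cox proportional hazards model for time-to-event endpoints".
- **Primary outcome measure.** By contrast, time to clinical improvement runs "until a decline of two categories on a six-category ordinal scale of clinical status", or to live discharge.
- **Discussion.** The article says that "we have included a range of secondary endpoints to show consistency with the primary endpoint".

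**The concern.** An outcome named improvement should record a change. Here a patient who enters at NEWS2 2 or below and stays there for 24 h meets the definition at about day 1 having changed in nothing. The sections on eligibility, outcome assessment, analysis, subgroups and missing data contain no rule that removes or reclassifies such a patient.

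These events would occur at about the same rate in both arms, because baseline NEWS2 is independent of allocation, and they carry almost no information on treatment. In a Cox model they dilute the estimated hazard ratio. The secondary outcomes are meant to show consistency with the primary endpoint, and the primary endpoint does not have this feature. A weaker result on disease improvement could therefore arise partly from the definition and be misread as disagreement.

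**Working it through.** The protocol gives no figure for this outcome, so there is nothing to reproduce. The check has two parts: whether the situation can arise, and how much it would matter.

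**1. Can an eligible patient be at 2 or below?** The documents alone do not settle this, because they do not print the scoring. Assume the usual NEWS2 points: SpO2 of 96% or more = 0, 94–95% = 1, 92–93% = 2; supplemental oxygen = 2.

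- Room air, SpO2 92–94%, other signs normal: total 1 or 2. This patient meets the SpO2 criterion.
- Low-flow oxygen, SpO2 96% or more, other signs normal: 2 + 0 = 2. This patient can qualify through PaO2/FiO2, or through an earlier room-air reading.

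Both would be at the threshold on entry. The 24 h condition screens out only those whose score then rises above 2.

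**2. How large is the dilution?** Inputs:

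- 453 patients, 302 on remdesivir and 151 on placebo (Sample size {14}).
- Hazard ratio 1.4 among patients above the threshold, borrowed from the primary endpoint, for which the article gives "a reduction in TTCI to 15 days on remdesivir if the TTCI on standard of care was 21 days" (21/15 = 1.4).
- Share *f* already at 2 or below: not in the documents; taken as 5%, 10%, 20% and 30%. Each such patient has an event on day 1 in either arm.
- Remaining patients: exponential times, censored at day 28.

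Two Cox simulations were run. Simulation A set the day-28 event proportion at about 80% (400 trials per value). Simulation B used medians of 15 and 21 days (300 trials per value). In B the event proportions are 1 − 2^(−28/15) = 0.726 and 1 − 2^(−28/21) = 0.603, or (302 × 0.726 + 151 × 0.603)/453 = 0.685 overall.

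| *f* | Patients (453 × *f*) | HR, A | Mean Z, A | HR, B | Power, B (one-sided 2.5%, fixed sample) |
|---|---|---|---|---|---|
| 0 | 0 | 1.39 | 2.92 | 1.39 | 76% |
| 5% | 23 | 1.37 | 2.80 | 1.37 | 73% |
| 10% | 45 | 1.35 | 2.68 | 1.34 | 69% |
| 20% | 91 | 1.30 | 2.36 | 1.28 | 54% |
| 30% | 136 | 1.25 | 2.03 | 1.21 | 41% |

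**Hand check.** If day-1 events contribute a log hazard ratio of zero, the pooled log hazard ratio is roughly ln(1.39) × (1 − *s*). Here *s* = *f* / [*f* + (1 − *f*)*E*] is the share of events that carry no contrast, and *E* is the event proportion in the rest.

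- *f* = 10%, *E* = 0.80: *s* = 0.10/(0.10 + 0.72) = 0.122; HR ≈ exp(0.329 × 0.878) = 1.34.
- *f* = 30%, *E* = 0.80: *s* = 0.30/(0.30 + 0.56) = 0.349; HR ≈ exp(0.329 × 0.651) = 1.24.
- *f* = 30%, *E* = 0.685: *s* = 0.30/(0.30 + 0.479) = 0.385; HR ≈ exp(0.329 × 0.615) = 1.22.

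These lie within about 0.02 of the simulated values.

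**Size against sampling error.** With 0.80 × 453 ≈ 362 events and 2:1 allocation, the standard error of the log hazard ratio is 1/√(362 × 2/9) = 0.111. In simulation A the shift is:

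- 5%: ln(1.39/1.37) = 0.0145, or 0.13 standard errors.
- 10%: ln(1.39/1.35) = 0.029, or 0.26 standard errors.
- 20%: ln(1.39/1.30) = 0.067, or 0.60 standard errors.
- 30%: ln(1.39/1.25) = 0.106, or 0.95 standard errors.

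**The case against.** **The affected share may be small.** The Abstract describes patients with signs or symptoms of severe pneumonia and radiological confirmation, and entry also requires imaging-confirmed pneumonia. A patient with otherwise normal vital signs fits that picture poorly. This stands, and it is why the size is shown as a range. Neither requirement is a NEWS2 floor, however, and patients without oxygen support are expressly provided for.

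**The mechanism needs a scoring table that is not in the documents.** This stands. A reader might infer that, because no NEWS2 minimum is stated, entry at 2 or below is possible under any scoring. That does not follow: if the oxygenation item alone gave 3 points, the entry criterion would itself act as a floor. The point rests on the assumed scoring.

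**The simulations are illustrative.** They borrow the effect and event rate of a different endpoint and assume that every patient at 2 or below stays there for 24 h. They also differ from each other at 20–30%. All of this stands: the direction is firm, but the numbers depend on the inputs.

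**An absolute stability threshold is a legitimate complement to a change-based primary endpoint, and the SAP may deal with patients at threshold on entry.** The first half stands as a matter of choice. The second does not remove the point. The article states the event rule itself, and as stated it counts an unchanged patient as improved; a SAP rule to the contrary would alter the published outcome.

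**Conclusion.** The point holds as a defect in the definition of one secondary outcome. As written, disease improvement can be met at about day 1 by a patient who has not improved, provided the usual NEWS2 scoring applies and some enrolled patients start at 2 or below.

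The expected consequence is dilution. With a true hazard ratio of 1.4 in the other patients, the estimate moves by 0.02 at a 5% share, 0.04–0.05 at 10%, 0.09–0.11 at 20% and 0.14–0.18 at 30%. At 5–10% this is minor against sampling error. It becomes material only at shares that nothing in the documents supports or rules out.

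Three stronger readings are tempting but unsupported:

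- **Bias towards one arm.** Baseline status is balanced by randomisation in expectation, so early events are added to both arms alike. If there is no treatment effect, they leave the hazard ratio at 1.
- **Damage to the trial's main conclusion.** The primary endpoint requires a two-category decline or live discharge, and the stopping boundaries rest on it alone.
- **A key outcome compromised.** The article lists its secondary outcomes without ranking, and this one has no special status.

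**What to change.** Add one sentence to the outcome definition: the NEWS2 limb applies only to patients with NEWS2 above 2 at randomisation, and patients at 2 or below at baseline reach the outcome by live discharge only. Baseline NEWS2 can be derived from the vital signs that the participant timeline already schedules at screening, so no new assessment is needed.

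The cost is somewhat fewer and later events on this outcome. Further conditions, such as requiring the 24 h to be free of supplemental oxygen or a minimum fall in score, are a matter of preference and are not needed to close this gap. If they were offered as alternatives, a patient whose score fell enough could still qualify while on oxygen.
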